#### Patient health questionnaire [35]

The PHQ-9 is a self-report questionnaire corresponding to the DSM-IV diagnostic criteria for major depressive disorder. Each item is rated in frequency on a 4-point (0 = not at all, 3 = nearly every day) scale. Total scores range from 0 to 27 with higher scores reflecting higher levels of psychopathology. A PHQ-9 score of ≥10 is used as a clinical cut-off for probable DSM-IV diagnosis of MDD [36]. The PHQ-9 demonstrates good psychometric properties and has been used extensively to measure treatment outcomes during internet CBT interventions targeting depression and anxiety [37,38]. The PHQ9 will be administered at baseline, following the 1-week CBM intervention and at 1-month follow-up.

#### The word sentence association test for obsessive compulsive disorder [39]

The WSAO is a measure of interpretation bias in OCD, comprising of 20 distinct ambiguous obsessive-compulsive (OC)-related sentences across multiple domains of OC symptoms. Ten sentences are followed by an OC-related threat word and ten are followed by a benign word. Participants are instructed to indicate how related the sentence and the word are to each other. For example, participants see the sentence ‘Part of the floor you are walking on is brown*’* and then circle how related the sentence is to the word ‘excrement’ (threat word). Participants also see ambiguous sentences paired with benign words, such as ‘There were many appliances running when you left*’* and rate how related the sentence is the word ‘busy’. Higher ratings of relatedness for threat words to the ambiguous sentences compared to ratings of relatedness of benign words to the ambiguous sentences reveals a threat interpretation bias on this measure. Internal consistency is good (a = .81) for the total measure. The WSAO will be collected at baseline, following the 1-week CBM intervention, and at 1-month follow-up.

#### Kessler-10 psychological distress scale [40]

The K10 consists of 10 items ranked on a five point scale designed to measure non-specific psychological distress. For the current study, the time-frame was modified to assess psychological distress in the past week rather than in the past 30 days. The K10 possesses strong psychometric properties [40].

#### Diagnostic status

Change in diagnostic status will be indexed using the M.I.N.I. [32] Obsessive Compulsive Disorder (OCD) Module, administered at baseline and 1-month follow-up. All research personnel conducting diagnostic assessments will be blind to the baseline interview and will have received extensive training in administration of the M.I.N.I by a registered psychologist with PhD level qualifications.

### Data collection and management

Data for the primary and secondary outcome questionnaires are collected via the Virtual Clinic system software and Key Survey software licensed by UNSW. All information collected by the Key Survey and CBM software is coded with either a participant identification number or an email address to facilitate data-to-patient matching. Clinical information, including diagnostic status using the M.I.N.I., is collected by interview via telephone and stored in written format in a secure location at CRUfAD. Any identifiable information that is collected remains confidential, except as required by law. Only members of the site (CRUfAD) research team will have access to participant information and data.

To promote participant retention, participants are reminded that data collection is an important aspect of research and enables the research team to track their progress and to evaluate the program. Participants are offered one entry into a lottery for a gift card valued at $100 AUD in exchange for completion of the 1-month follow-up questionnaires. All data will be extracted from the CBM software servers in the form of either an SPSS output file or an Excel compatible file to be transferred to SPSS by a member of the research team. All data will be stored on a secure Virtual Clinic server.

Participants are informed in writing that the research team will plan to publish the results of the trial in peer-reviewed scientific publications and presentations. Participants are informed that in any publication or presentation, information will be provided in such a way to maintain anonymity. All members of the research team who provide intellectual input to the trial design, execution, or write-up will be acknowledged as an author on any publications. Participants will be sent (via email) a written summary of the results in lay terms following completion of the trial study phase.

### Statistical methods

Significance testing of group differences regarding demographic data and pre-treatment measurements will be conducted using ANOVA and χ2 where the variables consist of nominal data. Intent-to-treat (ITT) mixed models using restricted maximum likelihood (REML) estimation will be used to account for missing data due to participant drop-outs. Significant effects will be followed up with pairwise contrasts comparing pre-treatment to post-treatment scores. Complete-case analyses of the primary hypotheses using data from participants who complete all four sessions of the CBM program will also be conducted. The effect of potential treatment moderators will be evaluated by including baseline variables of interest as a covariate and interaction term in separate mixed models analyses. Analyses will be performed in SPSS. Effect sizes will be calculated between groups (Hedges *g*) and within groups (Cohen’s *d*, adjusting for the repeated measures correlation) using the pooled standard deviation and adjusted for sample size.

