**Methods/Design:**

Patients meeting diagnostic criteria for a current or lifetime diagnosis of OCD will be recruited via the research arm of a not-for-profit clinical and research unit in Australia. The minimum sample size for each group (alpha set at 0.05, power at .80) was identified as 29, but increased to 35 to allow for 20% attrition. We will measure the impact of CBM on interpretations bias using the OC Bias Measure (The Ambiguous Scenarios Test for OCD ;AST-OCD) and OC-beliefs (The Obsessive Beliefs Questionnaire-TRIP; OBQ-TRIP). Secondary outcome measures include the Dimensional Obsessive-Compulsive Scale (DOCS), the Patient Health Questionnaire (PHQ-9), The Kessler Psychological Distress Scale (K10), and the Word Sentence Association Test for OCD (WSAO). Change in diagnostic status will be indexed using the OCD Mini International Neuropsychiatric Interview (M.I.N.I) Module at baseline and follow-up. Intent-to-treat (ITT) marginal and mixed-effect models using restricted maximum likelihood (REML) estimation will be used to evaluate the primary hypotheses. Stability of bias change will be assessed at 1-month follow-up.

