### Hypotheses

For participants who meet diagnostic criteria for current OCD, we predict that CBM active training, relative to CBM control training, will result in a bias towards more positive OC-specific targets and a reduction in OC symptom measures. We further predict that benefits will be maintained at 1-month follow-up. For participants who meet criteria for a lifetime diagnosis of OCD (and do not meet criteria for current OCD) and who evidence a negative interpretation bias at baseline, we predict that CBM active training, relative to CBM control training, will result in a bias towards more positive OC-specific targets (OCD-Bias measure) and bias scores (AST-OCD; WSAO). We do not predict a significant change in measures of OC symptoms (DOCS) in individuals with a lifetime diagnosis.

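### The only contrast the plan names is pre- versus post-treatment, after an unspecified significant effect; the between-arm contrasts that would test the hypotheses, at post-treatment and at 1 month, are not named

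*Protocol article*

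**What the plan says.** The Hypotheses section makes a between-arm prediction for participants with current OCD: "CBM active training, relative to CBM control training, will result in a bias towards more positive OC-specific targets". It then adds a claim about durability: "We further predict that benefits will be maintained at 1-month follow-up". The Trial design section describes a two-arm parallel superiority trial, and the sample size under Participants and recruitment rests on between-group effect sizes of 0.66 and 0.76.

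The Statistical methods section gives the main analysis as follows: "Intent-to-treat (ITT) mixed models using restricted maximum likelihood (REML) estimation will be used to account for missing data due to participant drop-outs". It lists no fixed effects, no time points and no tested term. The next sentence contains the only contrast in the article: "Significant effects will be followed up with pairwise contrasts comparing pre-treatment to post-treatment scores". Between-group Hedges g and within-group Cohen's d are both planned, with no time point attached.

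The abstract says that "mixed-effect models using restricted maximum likelihood (REML) estimation will be used to evaluate the primary hypotheses", and that "Stability of bias change will be assessed at 1-month follow-up".

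On baseline data, the Statistical methods section says: "Significance testing of group differences regarding demographic data and pre-treatment measurements will be conducted". Baseline covariates are mentioned only for separate moderator models. No baseline adjustment is stated for the main model.

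**The concern.** A pre-to-post contrast measures change in whichever group it is applied to. It does not estimate active minus control. Change in both arms is plausible here: half of the control scenarios resolve positively, and the same bias measures are given three times. Improvement in the active arm is therefore weak evidence of efficacy. Comparing the significance of two within-arm tests is a well-known route to a false claim.

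The trigger is also open. The sentence does not say which significant effect leads to the contrasts, so a main effect of time, which both arms can produce together, would satisfy it. For 1 month there is a hypothesis and a commitment to assess stability, but no named contrast that would decide the question.

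Precision is a further issue. The baseline score is collected on every participant, but its use in the main comparison is not stated.

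**Working it through.** **The plan's own figure.** The stated minimum is 29 per group at alpha 0.05 and power 0.80. A two-sided two-sample t-test with d = 0.76 needs 29 per group (power 0.812), so the figure reproduces with the larger of the two cited effects. It is a between-arm calculation, so the trial was sized for a comparison that the contrast sentence does not name. Enrolment of 35 per group with 20% attrition leaves 35 × 0.80 = 28, which is used below.

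**Step 1. Two within-arm tests when the arms do not differ.** Assumptions not in the documents: both arms have the same true standardised within-person change dz (mean change divided by the SD of change) of 0.3, 0.4 or 0.5; the arms are independent; a two-sided paired t-test at 0.05 is run in each arm with n = 28. If p is the power of one paired test, the chance that active is significant and control is not equals p(1 − p).

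| dz | p | p(1 − p) |
|---|---|---|
| 0.3 | 0.334 | 0.334 × 0.666 = 0.223 |
| 0.4 | 0.532 | 0.532 × 0.468 = 0.249 |
| 0.5 | 0.723 | 0.723 × 0.277 = 0.200 |

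**Step 2. Add the gate.** The contrasts follow a significant effect, so the pattern must be counted jointly with that effect. Simulation of the same setting (200,000 runs per row):

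| dz | No gate | Pattern and significant time effect | Pattern and significant group-by-time |
|---|---|---|---|
| 0.3 | 22% | 19% | 2.3% |
| 0.4 | 25% | 23% | 2.4% |
| 0.5 | 20% | 20% | 2.2% |

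Gating on time gives almost no protection. Gating on group-by-time brings the pattern to about 2%. The published sentence allows either.

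**Step 3. What baseline adjustment is worth.** Take unit variance at each visit and pre-post correlation r (assumed 0.5 to 0.7; the documents give none). With complete data and unconstrained baseline means, the group-by-time contrast from pre to post in a repeated-measures model equals a comparison of change scores. Per-person variances are:

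- change score: 2(1 − r)
- baseline-adjusted: 1 − r²
- ratio, adjusted to change: (1 + r)/2

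At r = 0.5 these are 1.00 and 0.75, a ratio of 0.75 and a saving of 25%. At r = 0.7 they are 0.60 and 0.51, a ratio of 0.85 and a saving of 15%.

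In power terms at d = 0.66, n = 28 per arm and r = 0.5: the change score has effective d = 0.66/√1.00 = 0.66 and power 68%; the adjusted analysis has effective d = 0.66/√0.75 = 0.762 and power 80%. At r = 0.7 the effective values are 0.66/√0.60 = 0.852 and 0.66/√0.51 = 0.924, with power 88% and 92%, so the gain is smaller.

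**The case against.** The strongest reply is that the contrasts are follow-up probes, not the efficacy test. The abstract assigns the primary hypotheses to the mixed models, those hypotheses are between-arm, and between-group effect sizes are planned. A group-by-time term would be the between-arm test, and looking at within-arm change after a significant interaction is ordinary practice. A journal article also leaves much model detail to fuller documents. Most of this stands, and it limits the finding. It does not remove it, because the article does fix one contrast, that contrast does not match the hypothesis, and its trigger is left open.

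Three stronger readings are tempting, and the documents do not support them:

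- *Efficacy will be claimed from significance in one arm but not the other.* Nothing says so. The contrasts come after a model test and do not replace it. The ungated 20% to 25% therefore should not be quoted alone.
- *The plan skips 1 month.* The abstract commits to assessing stability then, and the bias, belief and symptom questionnaires for which the article gives a schedule are collected at that visit. What is missing is a named contrast.
- *Baseline significance tests are used in place of adjustment.* The article does not link the two. It states no adjustment for the main model, which is silence, not exclusion. A repeated-measures model with pre-treatment as a time level does use baseline, though without constrained means it does so as a change score. An unadjusted analysis is valid under randomisation; the loss is precision.

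The baseline tests are a minor matter. Under randomisation they test only chance, but no decision in the plan depends on them.

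**Conclusion.** The concern holds as a mismatch between the stated hypotheses and the only stated contrast. The article names no between-arm contrast at post-treatment or at 1 month, and it does not say which effect triggers the pre-to-post comparisons. Depending on that trigger, a misleading within-arm pattern would occur about 20% of the time (time main effect) or about 2% (group-by-time). Both figures assume equal true change of 0.3 to 0.5 within-person SD and 28 per arm. Adding baseline adjustment would save 15% to 25% of the variance relative to a change score, at assumed correlations of 0.7 to 0.5. It is not shown that the trial would reach a wrong conclusion; the wording permits a weak route to one and leaves the maintenance hypothesis without a matching contrast.

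**What to change.** Replace the contrast sentence with wording to this effect: the primary test is the between-arm difference at post-treatment (Day 8) from the mixed model, adjusted for the baseline score, either as a covariate or by constraining the arm means to be equal at baseline; the same between-arm contrast at 1 month addresses maintenance; neither is conditional on an omnibus test or a time effect; within-arm pre-to-post changes are descriptive.

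As a minor companion change, present baseline characteristics by arm descriptively, without significance tests.

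The cost is analysis wording. No new data, visits or software are needed. The Trial status section reports 28 participants randomised at submission and data collection aimed to finish in June 2015, so at that point the change could have been made before any outcome analysis.

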### Monitoring

The clinical trials manager of CRUfAD and a member of the research team will oversee data collection and monitoring. An interim analysis will only be conducted to check that the planned number of participants have been retained in the trial following enrollment. Any adverse events will be reported to the head of CRUfAD and to the HREC of St. Vincent’s Hospital, the responsible body for initiating a clinical trial audit.

### Ethics and dissemination

The current trial protocol has been approved by the Human Research Ethics Committee (HREC) of St. Vincent’s Hospital and the University of New South Wales, Sydney. The trial is registered as ACTRN12613001130752. No protocol amendments have been made.

## Discussion

The current randomized controlled trial will provide a test of the utility of a CBM intervention in modifying maladaptive negative interpretation biases associated with OCD. The acceptability of CBM as a credible treatment is still unknown. Although a qualitative study suggests CBM-I (targeting social anxiety) is acceptable to patients, the tasks may need refining to enhance engagement [41]. In the current study, outcome measures will focus on interpretative bias and OC symptomology; a limitation of the online nature of the study is the inability to include a behavioral outcome measure (OC-stressor task). While CBM-I interventions have been linked to subsequent reductions in anxiety [28] and more adaptive physiological responding during OC stressor tasks [29], change in behavioral responses has not yet been demonstrated. Reviews such as those by Beard [1] and Hallion and Ruscio [2] argue the importance of future studies including both behavioral and neural outcome measures to ascertain the true scope of CBM-I interventions.

## Trial status

This article was submitted on 6 January 2014. To date, 28 participants have met eligibility requirements and been randomized to treatment condition. The first round of applications opened on 24 October 2013 and the first participant was enrolled on 25 October 2013. Data collection aims to be complete in June 2015.

## Abbreviations

CBM: cognitive bias modification; OCD: obsessive compulsive disorder; ITT: intent-to-treat; AST-OCD: The Ambiguous Scenarios Test for OCD; OBQ-TRIP: the Obsessive Beliefs Questionnaire; DOCS: Dimensional Obsessive-Compulsive Scale, PHQ-9, the Patient Health Questionnaire, K10, the Kessler Psychological Distress Scale; WSAO: the Word Sentence Association Test for OCD; M.I.N.I: Mini International Neuropsychiatric Interview, CBM-A, attentional bias; CBM-I: interpretive bias.
